## Abstract

**Background:**

The relative number of children meeting the minimal required dose of daily physical activity remains execrably low. It has been estimated that in 2015 one out of five children will be overweight. Therefore, low levels of physical activity during early childhood may compromise the current and future health and well-being of the population, and promoting physical activity in younger children is a major public health priority. This study is to gain insight into effects of a Physical Education based playground program on the PA levels during recess in primary school children aged 6-12.

**Methods/design:**

The effectiveness of the intervention program will be evaluated using a prospective controlled trial design in which schools will be matched, with a follow-up of one school year. The research population will consist of 6-12 year old primary school children. The intervention program will be aimed at improving physical activity levels and will consist of a multi-component alteration of the schools' playground. In addition, playground usage will be increased through altered time management of recess times, as well as a modification of the Physical Education content.

**Discussion:**

The effects of the intervention on physical activity levels during recess (primary outcome measure), overall daily physical activity and changes in physical fitness (secondary outcome measures) will be assessed. Results of this study could possibly lead to changes in the current playground system of primary schools and provide structured health promotion for future public health.

**Trial registration:**

Netherlands Trial Register (NTR): NTR2386

## Background

The health benefits of an active lifestyle are well established [1-5]. Sedentary lifestyle habits are a major international and Dutch Public Health (PH) problem [1]. A recent study in the Netherlands revealed that less than 10% of the children in primary schools (ages 4 through 11 years) achieve 30 minutes of physical activity (PA) per day [6], while the guidelines state a minimum of 60 minutes of PA per day for children in this age range [7]. Although between the ages 12 and 17 this percentage triples to around 30%, the number of children meeting the minimal required dose of daily PA remains execrably low. In addition, children's PA has been identified as a modifiable risk factor for lifestyle related diseases such as coronary heart disease [7,8] and osteoporosis [7,9]. Therefore, low levels of PA during early childhood will compromise the current and future health and well-being of the population [10], and promoting PA in younger children is a major PH priority [1,6].

Schools have been recognized as key settings in promoting PA [6,10-13]. Next to the home, the school is the environment where children spent most of their time [6,11-13]. Within the school, physical education (PE) lessons and recess (i.e. regular playtime breaks) represent the two main contexts in which children have the opportunity to be physically active [6,11-13]. Next to such structured and frequent PA opportunities, schools can cater irregularly for sporting days and other extracurricular activities (e.g. swimming). For the promotion of PA in the school setting, interventions targeted at recess have an important advantage over other interventions. While other physical activities provided by the school are on an irregular or non-daily basis, during recess all children have the opportunity to be physically active every single day. In addition, it has been suggested that younger children are more likely to participate in moderate to vigorous PA within unstructured play settings as opposed to more structured contexts [14].

To stimulate PA in children different playgrounds in Dutch neighborhoods have been developed (e.g. Cruyff Court, Krajicek Playground, Nike Zone Parc). At these playgrounds children have an energy expenditure of about 206 kcal/hour and participate in moderate to vigorous PA 35% of the play time [15]. Unpublished pilot research for this study on other, not specifically stimulating, playgrounds show that children participate in moderate to vigorous PA 10-30% of the play time. One of the stimulating playgrounds, Nike Zone Parc, is placed on the school grounds to stimulate PA in children, but this playground costs about Euro 50.000.

Research in the United Kingdom in children aged 4-11 years, showed that the application of simple multicolored markings on the school's playground significantly increased children's participation in moderate and vigorous physical activities on both the short-term [12] and long-term [13]. In addition it was found that children who were less active at baseline benefited more from this intervention than their more active peers.

Such a simple and cheap intervention has great potential also in the Dutch setting. A recent Dutch study revealed that in primary school-aged children, PA levels are below recommended guidelines [6]. This especially holds true for neighborhoods in which the part of the population consisting of immigrants is relatively high [16]. The lower PA levels are suggested to be due to the lower level of participation in organized sports and PA. The latter is a major issue for girls, while they may not participate in organized sports and PA due to their religious or cultural beliefs. The ability to give such groups of children the opportunity to be physically active on a daily basis during school recess has great potential PH gain. Next to descriptive information, this Dutch study [6] also described that children in primary schools prefer a re-structuring of school playgrounds in order to make better use of the playground. In addition, the PE teacher has the ability to support physical activity further by linking the playground to the PE curriculum [15].

In this study playground alterations in combination with a supporting PE program will be evaluated.

### Objective

The objective of this prospective controlled trial is to gain insight into effects of a PE based playground program on the amount and level of PA in primary school children aged 6-12.

This overall aim can be subdivided into five research questions that will be addressed in this study:

(1) What is the effect of the playground program on the amount and level of PA during recess in primary school children aged 6-12?

(2) What is the effect of the playground program on the amount and level of daily PA in primary school children aged 9-12?

(3) What is the effect of the playground program on physical fitness in primary school children aged 9-12?

(4) Are there differences in the effect of the playground program on PA levels for children of different ages?

(5) Are there differences in the effect of the playground program in PA levels for boys and girls?

## Methods/Design

The CONSORT statement was followed to describe the design of this study [17].

This statement provides a checklist intended to improve the quality of reporting randomized controlled trials.

### Hypothesis

It is hypothesized that recess PA levels will increase as a result of the intervention. In addition, an increase in the amount of daily PA is hypothesized. As a result of the positive effects mentioned above, overall fitness is expected to improve. It is hypothesized that boys have higher PA levels than girls [15] and that PA levels of younger children will be increased more as a result of the intervention than PA levels of older children [15].

### Study outline

The PLAYground study is a prospective controlled trial with a follow-up of one school year (corresponding to approximately 9 months) in a group of about 1,200 children from 8 primary schools. Intervention and control schools will be matched according to number of pupils, geographical location, playground size and usage of the playground before the intervention.

Baseline measurements for playground usage take place before the curricular year (June), baseline measurements for fitness and overall PA take place at the start of curricular year (September). Follow-up measurements for PA take place in January (mid-year) and in June (end of the curricular year). Follow-up measurements for fitness and overall PA will also take place in June.

The study is funded by the board of the schools, the Stichting Westelijke Tuinsteden (STWT) and by the Academy of Physical Education, Technical University of Applied Sciences of Amsterdam (ALO). The study design, procedures and informed consent procedure are approved by the Medical Ethics Committee (2010/222; NTR2386) of the VU University Medical Centre, the Netherlands.

The research population will consist of 6-12 year old primary school children. All children at the participating schools will participate in this study following passive informed consent as has been used in comparable studies [18,19]. Schools will inform all parents on the study goals and procedures. If a parent does not want their child(ren) to participate in the study, this can be indicated, after which the child will be excluded from the study population.

### Sample size

For the power analysis data from a previous descriptive study on PA during school recess in primary schools was used [20]. This study showed that at most 40% of the children participate in at least moderate PA during school recess. Results from a pilot study revealed that a doubling of the percentage of children participating in at least moderate PA is feasible. In order to establish such an effect with a power of 90% and an alpha of 0.05, a total sample of 64 children split across two groups is needed.

While schools will serve as intervention units ideally a cluster effect should be taken into account when establishing group size. Assuming an intra-cluster correlation coefficient of 10% a study sample consisting of 8 schools (4 intervention schools and 4 control schools) is required. Based upon a careful low-end estimate of approximately 150 participating children attending at these primary schools, this will result in a sample of about 1,200 children.

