#### Accelerometers

PA will be measured using accelerometers (ActiGraph ActiTrainer), which are a reliable and valid objective PA measurement tool for children and adolescents [22]. During the researchers' fortnight visit of the schools, a total of 40 children of all ages (8 per grade) will be randomly chosen to wear an accelerometer during the school day. This is an arbitrarily chosen number, based upon the organisational ability to perform these measurements on a single day by the available research staff. The Actitrainer will be set at an epoch of 1 second to measure every change in intensity and the display will be turned off, so children will not be distracted by the Actitrainer. The Actitrainer will be called a 'growing meter' or a 'honesty meter', so children will not be stimulated to be more active just because of wearing the Actitrainer.

Through these measurements it is possible to objectively register intensity and duration of PA during recess. Existing analytical CSA programs (e.g. MAHUffe) are not usable to analyse the thus obtained data, as recess time only lasts 15 minutes. These current commercial programs are set to analyse PA during a prolonged period of time, e.g. 5 consecutive days. For this reason a dedicated Matlab program to analyse the number of counts during the short recess time was written. This Matlab program analyses the counts per minute for every child, and combines the resulting data with date of measurement, total time of measurement and grade, age and sex of the child.

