### Statistical analyses

The effectiveness of the PLAYground intervention will be analysed by means of a multilevel regression analysis with the outcome measures at follow-up (9 months) as the dependent variables and adjusting for the baseline levels of the outcome measure. Both crude and adjusted analyses will be performed. Regression analyses will be performed using SPSS 18.0 (SPSS Inc. Chicago, Illinois, USA). For all analyses a two-tailed significance level of < 0.05 will be considered statistically significant.

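### The stated 90% power with 8 schools treats the between-school variance as known; on 6 degrees of freedom it is about 84–90% at 150 children per school and 78–85% at 40

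*Protocol article*

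**What the plan says.** The Sample size section of the protocol article takes its control rate from a descriptive study: "This study showed that at most 40% of the children participate in at least moderate PA during school recess". It takes its effect from a pilot, where "a doubling of the percentage of children participating in at least moderate PA is feasible". From these it concludes that "with a power of 90% and an alpha of 0.05, a total sample of 64 children split across two groups is needed". It then turns to clustering: "Assuming an intra-cluster correlation coefficient of 10% a study sample consisting of 8 schools (4 intervention schools and 4 control schools) is required". The size of each school enters only afterwards, as "approximately 150 participating children attending at these primary schools, this will result in a sample of about 1,200 children".

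The Accelerometers section gives a different number for the children measured. At each fortnightly visit to a school, "a total of 40 children of all ages (8 per grade) will be randomly chosen to wear an accelerometer during the school day". Of the 40 it says: "This is an arbitrarily chosen number, based upon the organisational ability to perform these measurements on a single day by the available research staff".

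The Study outline says that intervention and control schools are matched on four factors. It places the end-of-year measurement of physical activity in June. The Statistical analyses section specifies a multilevel regression on the 9-month outcome, adjusted for baseline, and adds: "For all analyses a two-tailed significance level of < 0.05 will be considered statistically significant". It names neither a reference distribution nor a degrees-of-freedom method, and it does not say whether the matching enters the model.

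**The concern.** Whole schools receive the intervention or do not. The effect is therefore judged against the variation between school means, and that variation has to be estimated from only eight schools. A calculation that inflates an individual-level sample for clustering and stops there uses normal quantiles, as if the between-school variance were known. With many clusters this hardly matters. With 4 against 4 the two-sided 5% critical value is 2.45 rather than 1.96, and power falls noticeably.

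The section also does not connect its 150 children per school with the 40 who wear an accelerometer on a given day. Those 40 bear directly on the primary outcome, physical activity during recess. If the 90% is relied on as it stands, a null result would be read as stronger evidence against the programme than eight schools can provide.

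**Working it through.** **Inputs.** From the Sample size section: control rate 0.40, intervention rate 0.80, power 90%, alpha 0.05, intra-cluster correlation 0.10, 4 schools per arm, about 150 children per school. From the Accelerometers section: 40 children per school per visit. From the Statistical analyses section: two-sided testing. My assumptions: a binary outcome, equal school sizes, and no gain from baseline adjustment or matching.

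**Reproducing the 64.** With mean proportion 0.6, the common variance per child is 0.6 × 0.4 = 0.24. Then n per arm = 2 × 0.24 × (1.960 + 1.282)² / 0.40² = 0.48 × 10.51 / 0.16 = 31.5, rounded up to 32, or 64 in total. This matches exactly. Some other common formulas give other totals (60 with the pooled-null form or the arcsine, 70 with continuity correction, 54 with unpooled variances), so 0.24 is the variance that reproduces the printed figure.

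**Reproducing the 8 schools.** The article prints no design effect. Taking the usual one, 1 + (m − 1) × 0.10:
- m = 40: design effect 4.9; 32 × 4.9 / 40 = 3.92 schools per arm.
- m = 150: design effect 15.9; 32 × 15.9 / 150 = 3.39 schools per arm.

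Both round up to 4 per arm, so the 8 schools reproduce at either size. The result does not show which m was used. Neither line allows for the number of schools.

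**Allowing for 6 degrees of freedom.** The variance of the difference is SE² = V × [1 + (m − 1) × 0.10] / (4m). Here V is the sum of the two per-arm variances: V = 0.48 for the variance behind the 64, and V = 0.4 × 0.6 + 0.8 × 0.2 = 0.40 with unpooled variances. The noncentrality is 0.40 / SE. Power comes from the noncentral t distribution on 4 + 4 − 2 = 6 degrees of freedom, critical value 2.447.

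| Children per school | V | SE | Noncentrality | Power, normal theory | Power, 6 df |
|---|---|---|---|---|---|
| 40 | 0.48 | 0.121 | 3.30 | 91.0% | 78.4% |
| 40 | 0.40 | 0.111 | 3.61 | 95.1% | 85.1% |
| 150 | 0.48 | 0.113 | 3.55 | 94.4% | 83.8% |
| 150 | 0.40 | 0.103 | 3.89 | 97.3% | 89.6% |

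The normal-theory column exceeds 90% throughout, and the 6-df column falls below it throughout. Beta-binomial simulation of school means gave about 82% at 40 and 87% at 150, inside these ranges.

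**Ceiling.** As m grows without limit, SE² tends to V × 0.10 / 4. With V = 0.48 the noncentrality tends to 3.65 and power to 85.8%. With V = 0.40 they tend to 4.00 and 91.2%, and 90% is reached at about 200 children per school. On the variance behind the 64, measuring more children therefore cannot restore 90% with eight schools.

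**If analysed as four matched pairs.** Degrees of freedom are 4 − 1 = 3, critical value 3.182. With the same noncentralities and no credit for matching, power is 60.5% (V = 0.48) to 67.7% (V = 0.40) at 40 children, and 66.2% to 73.3% at 150.

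**Reference distribution.** If the treatment coefficient were judged against 1.96 with a variance estimated on 6 df, the type I error would be 2 × P(t₆ > 1.96) = 9.8%. Simulated REML fits at correlation 0.10 gave 9.7% at 40 per school and 9.8% at 150.

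**The case against.** Four arguments stand against a stronger reading.

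- **A flat 85%.** A reader might infer that power is simply about 85% because 40 children per school are measured. The text does not support that. Forty is a per-visit number, visits are fortnightly, and the article does not say how many distinct children contribute at 9 months. Two visits with entirely different children would give 80 per school and 82.1% to 88.2%. At 150 with unpooled variances the shortfall is under half a point. This argument stands, so only a conditional range can be given. It does not remove the point: the outcome analysed is the end-of-year one, and the article does not connect 150 children per school with 40 per measuring day.
- **A design effect for 150.** A reader might infer that the 64 was multiplied by a design effect for 150. None is printed, and 40 and 150 both lead to 8 schools.
- **Inflated type I error.** A reader might infer that the planned test runs at nearly twice its nominal level. The Statistical analyses section names no normal or Wald test, and the degrees-of-freedom method is commonly left to an analysis plan. The 9.8% describes one possible implementation, so it is a risk to guard against and not an error in the text.
- **Baseline adjustment and matching.** Adjusting for baseline would raise power, and matching may reduce between-school variance. Both could offset the loss. The power statement claims credit for neither, however, and a pair-matched analysis costs 3 of the 6 degrees of freedom.

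**Conclusion.** The concern holds in conditional form. The 64 children and 8 schools are arithmetically reproducible, but the 90% attached to them requires the between-school variance to be known. At the plan's own effect and intra-cluster correlation, an unmatched and unadjusted comparison has about 84–90% power if 150 children per school supply the 9-month outcome, and about 78–85% if 40 do. In each range the lower figure is the one consistent with the printed 64, and on that variance eight schools cannot exceed 85.8%. The loss against the stated 90% thus runs from negligible to about 12 points, depending on choices the article leaves open. All these figures take 40% against 80% at face value, although the article gives the 40% as a maximum. They also assume a binary outcome and equal school sizes.

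**What to change.** In the Sample size section, restate power on between-school degrees of freedom as a range with its conditions: the number of children per school, the variance used, and no credit for baseline adjustment or matching unless that credit is justified. Say how many children per school supply the 9-month accelerometer outcome, and reconcile that number with both the 40 per visit and the 150 per school. Say whether the matching enters the analysis, since this decides between 6 and 3 degrees of freedom.

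As a safeguard, add that the treatment effect will be tested with small-sample degrees of freedom (Satterthwaite or Kenward-Roger), or by a t test on baseline-adjusted school means.

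The cost is a few sentences, with no change to recruitment or measurement. The stated power becomes less favourable, and confidence intervals will be somewhat wider than with a 1.96 multiplier (2.447 / 1.960 = 1.25 times as wide on 6 degrees of freedom).

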### Recruitment

The eligible research population will consist of 6-12 year old children (n = 1,200). The board of schools (STWT) and the management of the schools already gave their approval for this study. All of the participating primary schools in the urban area of Amsterdam are located in neighborhoods with a relatively large part of the population consisting of foreign descent immigrants.

The schools will be recruited through the STWT. All schools that are part of the STWT will be informed about the study. Interested schools may receive additional information, after which they are free to choose to participate. Intervention and control schools will be matched according to number of pupils, geographical location, playground size and usage of playground before intervention. Schools that participate as control school first, will be offered the same intervention after this study in the following curricular year, when proven effective.

For the determination of playground usage the playgrounds will be observed according to a validated standardised protocol (SOPLAY) [21], which consists of observations on the quantity of use of the playground in general, quantity of use of the playground by different groups of interest (e.g. age and gender), type of PA activities, intensity of PA, and aspects related to the physical environment (e.g. weather conditions, accessibility and teacher presence). With the SOPLAY protocol the playground will be scanned for child density and playground use every five minutes. One scan, including notation, takes one minute. The total observation takes one hour, which consists of 12 scans. To generate a reliable result for every playground 5 observations per playground will be done in different weather conditions.

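### Schools are matched but no random allocation is described, so which matched school is treated may depend on unmatched factors; a draw within pairs would fit the timetable and need no extra schools

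*Protocol article*

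**What the plan says.** The Abstract gives the design as a "prospective controlled trial design in which schools will be matched". Study outline and Recruitment name the same four matching features; the wording in Recruitment is "Intervention and control schools will be matched according to number of pupils, geographical location, playground size and usage of playground before intervention". Neither section says what decides which of the matched schools receives the intervention. The word for random choice is used only for sampling within schools, under Accelerometers: "a total of 40 children of all ages (8 per grade) will be randomly chosen to wear an accelerometer during the school day".

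On entry to the study, Recruitment says "Interested schools may receive additional information, after which they are free to choose to participate". On the control schools it says "Schools that participate as control school first, will be offered the same intervention after this study in the following curricular year, when proven effective".

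On timing, Study outline places the playground-usage baseline in June, before the school year, and Intervention places the painting in the summer holidays. Sample size plans four intervention and four control schools with an intra-cluster correlation of 10%. Statistical analyses plans a multilevel regression of the follow-up outcome, adjusted for its baseline level.

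**The concern.** The intervention depends heavily on people. According to the Intervention section, teachers join the play weekly, parents are invited monthly, and PE lessons are rebuilt around the playground. Staff motivation and parental support could plausibly influence both which school is treated and how recess activity develops over the year. Neither is among the four matching features.

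With four schools per arm, enrolling more children does not dilute a difference between schools. Baseline adjustment deals with differences in level that are already present. It does not deal with schools that would have changed differently over the year in any case. If such a difference lines up with the arms, part of a positive result could reflect the kind of school that was treated. This matters because the Discussion expects the results to inform changes to primary school playgrounds.

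**Working it through.** **Does a draw change the sample size?** Inputs from Sample size: 64 children before clustering, ICC 0.10, about 150 children per school.

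- Design effect: 1 + (150 − 1) × 0.10 = 15.9.
- Children: 64 × 15.9 = 1,017.6.
- Schools: 1,017.6 / 150 = 6.8, which becomes 8 in two equal arms, as the protocol states.

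The 64 is taken as given; nothing below depends on it. Drawing lots among the same eight schools leaves this figure unchanged.

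**What could a remaining imbalance do?** Inputs: ICC 0.10 and four schools per arm (Sample size), 40 children per school (the number measured at one visit, from Accelerometers), two-sided 5% test (Statistical analyses). Total child variance is set to 1, and the degrees of freedom are 8 − 2 = 6. The size of the imbalance is an assumption: *k* between-school SD left after matching and baseline adjustment, with no true effect.

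- SE of the arm difference: √(2 × (0.10 + 0.90/40) / 4) = √0.06125 = 0.247.
- Bias: *k* × √0.10 = *k* × 0.316.
- Rejection rate from the noncentral t distribution on 6 df, with noncentrality bias/SE:

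| *k* | Bias | Noncentrality | False rejection |
|---|---|---|---|
| 0.5 | 0.158 | 0.64 | 8.4% |
| 1 | 0.316 | 1.28 | 19.1% |
| 1.5 | 0.474 | 1.92 | 36.5% |

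With 150 children per school the SE falls to √(2 × (0.10 + 0.90/150) / 4) = 0.230 and the rates become 9.0%, 21.3% and 41.0%. More children per school therefore do not help against this bias.

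**What if the difference already shows at baseline?** Suppose the same one-SD difference is present at baseline and school means correlate *r* over time (an assumption). Adjustment leaves a bias of 0.316 × (1 − *r*) with SE 0.247 × √(1 − *r*²), on 5 df. For *r* = 0.5, 0.7 and 0.8 the noncentrality is 0.74, 0.54 and 0.43, and the false rejection rate is about 9%, 7% and 6%, against 19% without adjustment. The table above therefore applies only to imbalance that matching and baseline adjustment both miss.

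**What does a draw leave behind?** Four pairs give 2⁴ = 16 allocations. For a normally distributed unmatched school factor, the difference in arm means has an SD of √(2(1 − ρ)/4) between-school SD, where ρ is the within-pair correlation (assumed).

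- ρ = 0: SD 0.71; the chance of a difference above 0.5 SD is 48%.
- ρ = 0.7: SD 0.39; the chance is 20%.

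A pure within-pair randomisation test could not give a two-sided p below 2/16 = 0.125. The planned multilevel model does not rest on that test.

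**The case against.** The strongest reply is that this is a matched, baseline-adjusted controlled study that never calls itself randomised. One matching feature is prior playground use, observed with SOPLAY, which also records activity intensity. A standing difference in recess activity would therefore largely be visible at baseline, and the calculation shows that adjustment then removes most of the harm. This stands, and it confines the 8%, 19% and 36% to imbalance that does not show at baseline.

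Four stronger readings are tempting, and the article supports none of them.

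- **Schools choose their arm.** The freedom described in Recruitment concerns taking part. All eight schools are volunteers from one board, and no text says that schools, staff or the board pick the arm. What remains is that nothing rules it out.
- **Control schools receive the intervention anyway, so a draw costs them nothing.** The later offer is conditional on the intervention proving effective.
- **The article falsely presents the trial as randomised.** It says CONSORT was followed to describe the design, and of CONSORT that "This statement provides a checklist intended to improve the quality of reporting randomized controlled trials". That is a statement about reporting, not a claim that schools were randomised.
- **Pairs already exist.** The schools are matched, but one-to-one pairs are not mentioned, so forming pairs is part of the proposed change.

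It is also fair to say that a draw over so few schools does not ensure balance, and that the article gives no information on whether schools would accept one.

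**Conclusion.** The point holds as a weakness of the design. Schools are matched on four features, no random allocation is described, and factors on which the intervention depends are neither matched on nor removed by baseline adjustment unless they already show at baseline. The size cannot be known from the article. It ranges from close to nominal (about 8% false rejection at 0.5 between-school SD) to serious (about 36% at 1.5 SD), given ICC 0.10, 40 children per school, 6 df, and an imbalance that survives both matching and adjustment. For a difference already present at baseline, the one-SD figure falls from 19% to roughly 6–9% under the correlations assumed.

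A draw within pairs would remove systematic selection into arms with the planned eight schools. It would not guarantee comparable arms.

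**What to change.** **If schools are not yet assigned:** complete the June playground-usage baseline, form four matched pairs on the stated features, and have someone independent of the schools draw by lot which school of each pair is painted that summer. Say so in Study outline and Recruitment.

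**If allocation is already fixed:** state how it was made, report the trial as non-randomised and limit causal claims accordingly.

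**Cost:** four lots drawn between the June baseline and the summer painting, with the number of schools still 8. Schools give up any say over their arm, and control schools do so with only a conditional later offer. Playground designs, which follow each school's preference, must wait for the draw. Chance imbalance remains with four pairs, so school characteristics should still be reported by arm.
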